## Sample size

To the best of our knowledge, no study has assessed MVPA by actimetry at 12 months in patients with prostate cancer. Our hypotheses were formulated based on the results of the following. (1) Trinh *et al* have observed an initial mean level of MVPA 4.71±3.73 MET-hours/week in the exercise counselling and 6.96±7.72 MET-hours/week in the motivationally enhanced behavioural counselling group^27^ and 9.9 MET-hours/week at 3 months. (2) Livingston *et al* observed an increase of up to 12.5 MET-hours/week (>2 times the initial MVPA) at the end of the 3-month PA intervention.^15^ It is reasonable to think that a level of MVPA of between 12.5 and 7.5 MET-hours/week can be maintained at 6 months since peer support in our programme continues beyond the initial 3 months of PA. This level can be maintained at the end of 12 months of motivational support by the peer. Thus, if we estimate that we will observe the MVPA at 1 year of 5.5±4 MET-hours/week in the usual care group and 7.5±4 MET-hours/week in the Acti-Pair group, for an alpha risk of 5% and a power (1−β) of 90%, it is necessary to include 86 patients per group, that is, 172 in total. This calculation was performed using MedCalc software (MedCalc version 19.7). Assuming an intracluster correlation of 0.04 and an average cluster size of 58 participants, for 3 stepped-wedge steps, 346 patients per group will be needed, that is, 692 in total. If a drop-out rate of 10% is anticipated, a total of 762 patients will be needed.

Each peer will follow a maximum of 5 patients (Acti-Pair pilot study), and 381 patients will be followed (interventional group), that is, 77 peers. If we anticipate a drop-out rate of 10%, it will, therefore, be necessary to recruit 88 peers or 11 per department.

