### Data analysis

#### Quantitative outcomes analysis

The statistical analysis will be performed on the intention-to-treat population. The statistical significance will be a two-sided alpha level of 5%. Statistical analyses will be performed using SAS software (SAS-Windows version 9.4 on computer PC) and R software version 4.2.1 on computer. The characteristics of the population will be described using quantitative variables, including the mean and SD, and qualitative variables, such as the number of cases and percentages. The Acti-Pair programme’s effect on the PA level will be analysed using a mixed-effects model with a random intercept per department to consider the correlation of the level of PA between patients of the same department and a random effect on the initial value of PA. This random effect will depend on both the cluster and the patient (random effect of the patient nested in the cluster). The model will consider the fixed effect of the treatment group (Acti-Pair programme or usual care). The possible evolution of the evaluation criterion over time will be analysed by introducing a calendar time variable into the mixed-effects regression model (5 periods of 6 months, see figure 3). If a trend is identified, the calendar time variable can be introduced into the model as an ordinal variable. This analysis will make it possible to quantify the effect of the Acti-Pair programme after adjustment for a possible time effect. An interaction between the effect of the treatment group and the random ordinal by the department may be added to quantify any heterogeneity in the benefit of the Acti-Pair programme. An initial model will be built without additional adjustment. If an imbalance between the groups is observed, a second model will be built by adjusting the variable(s) on which the imbalance is observed (sensitivity analysis). A possible logarithmic transformation of the evaluation criterion could also be considered to satisfy the normality assumption of the linear mixed-effects model.

For the analysis of the secondary endpoints, no p value will be given, and only the 95% CIs of the efficacy indices will be estimated.^28^ It will be carried out using a mixed-effects model similar to the one used for the primary endpoint. No interim analysis is planned.

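### The 10% drop-out allowance is added to the required 692 instead of being divided out, so 762 recruits leave about 686 evaluable patients; power stays at about 90%.

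*Protocol article*

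**What the plan says.** The protocol's Sample size section builds the number in three steps.

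1. An individually randomised comparison of "5.5±4 MET-hours/week in the usual care group and 7.5±4 MET-hours/week in the Acti-Pair group", with the conclusion "for an alpha risk of 5% and a power (1−β) of 90%, it is necessary to include 86 patients per group, that is, 172 in" all. The Quantitative outcomes analysis section makes the test two-sided: "The statistical significance will be a two-sided alpha level of 5" per cent.
2. An adjustment for clustering and the stepped-wedge design: "Assuming an intracluster correlation of 0.04 and an average cluster size of 58 participants, for 3 stepped-wedge steps". The result is "346 patients per group will be needed, that is, 692 in total".
3. An allowance for loss: "If a drop-out rate of 10% is anticipated, a total of 762 patients will be needed".

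The next paragraph carries half of the final figure into the peer calculation, at up to five patients per peer: "381 patients will be followed (interventional group), that is, 77 peers". The article gives no other definition of drop-out and no inflation formula.

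**The concern.** The third step should turn a number needed at analysis into a number to recruit. If 10% of those recruited are lost, 90% of the recruited number must equal the requirement, so the requirement has to be divided by 0.90. The printed 762 looks like the requirement with 10% added, which falls short whenever the loss is 10%. What is at stake is whether the headline sample size, which the trial report will repeat, delivers the 692 patients that the same paragraph calls for, and whether the stated power and the peer numbers derived from it still hold.

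**Working it through.** **Inputs, all from the Sample size section except where noted.** Difference 7.5 − 5.5 = 2 MET-hours/week; SD 4; two-sided alpha 5% (sidedness from Quantitative outcomes analysis); power 90%; 86 per group (172 in total) before clustering; 346 per group (692 in total) after clustering; drop-out 10%; 762 in total and 381 in the intervention group after the allowance.

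**Step 1: reproduce the plan's figure.**
- Total: 692 x (1 + 0.10) = 761.2, rounded up to 762.
- Per group: 346 x (1 + 0.10) = 380.6, rounded up to 381; 2 x 381 = 762.

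Both printed figures are matched exactly, so the allowance was made by multiplication.

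**Step 2: what 762 delivers at 10% drop-out.**
- Total: 762 x 0.90 = 685.8, about 686. Shortfall: 692 − 685.8 = 6.2.
- Per group: 381 x 0.90 = 342.9, about 343 against 346.
- The drop-out rate at which 762 would leave 692 is 1 − 692/762 = 9.2%, not the stated 10%.

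**Step 3: the number that protects 692.**
- Total: 692 / 0.90 = 768.9, so 769.
- Per group: 346 / 0.90 = 384.4, so 385, or 770 for two equal groups.
- Difference from 762: 7 to 8 patients; 7/769 = 0.9% and 8/770 = 1.0%.

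**Step 4: effect on power.**
- Check of the starting point: with a standardised difference of 2/4 = 0.5, a two-sided 5% t-test with 90% power needs 85.03 per group, which agrees with the plan's 86.
- Design effect implied by the plan's own figures: 692/172 = 4.02, held fixed.
- At 692 evaluable: 692 / 4.02 / 2 = 86.0 effective patients per group; t-test power 90.3%.
- At 685.8 evaluable: 685.8 / 4.02 / 2 = 85.2 effective patients per group; t-test power 90.1%.
- The loss is about 0.25 percentage points. The normal approximation gives the same loss (90.6% to 90.4%).
- Exactly 90% by t-test needs 2 x 85.03 x 4.02 = about 684 evaluable, and 685.8 is above that.

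**Step 5: effect on peers.**
- 381/5 = 76.2, rounded up to 77; 385/5 = 77. There is no change.
- The 88 peers are 11 in each of eight departments, and this exceeds 77/0.90 = 85.6.

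**The case against.** The strongest reply is that the real requirement is 90% power, and 692 is only a rounded means to it. The plan took 85.03 up to 86, and that rounding covers the shortfall: about 684 evaluable patients give exactly 90%, and 762 recruits with 10% loss leave about 686. This stands. It means that the slip costs the trial none of its promised power.

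A second reply is that even 0.25 points may be too much. The number of departments is fixed at eight, so losing patients makes clusters smaller and lowers the design effect. As an illustration only, assume the simple design effect 1 + (m − 1) x 0.04. With m = 58 it is 3.28. If m shrinks in proportion, to 58 x 685.8/692 = 57.5, the loss is about 0.07 points. This also stands, as an indication of direction.

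A third reply is that the 10% rate, the ICC of 0.04 and the SD of 4 are themselves assumptions, with uncertainty well beyond 1%. That is fair on materiality, but it does not make the printed result follow from the printed inputs.

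Intention-to-treat analysis does not remove the point. The plan itself chose to allow for drop-out, and a patient lost before the 12-month actimetry supplies no primary outcome value.

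A reader might infer more than this: that the trial is underpowered, that more patients must be recruited, or that the peer target is wrong because it starts from 381. The documents support none of these. Power stays just above 90% under the plan's own inputs, and the peer number is 77 from either 381 or 385.

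**Conclusion.** The point holds as an arithmetic slip with a small consequence. The allowance was applied as 692 x 1.10 where the stated 10% drop-out calls for 692/0.90. The printed 762 therefore leaves about 686 evaluable patients, about 6 fewer than the section requires, and the recruitment figure is 7 to 8 patients (about 1%) too low for its stated purpose.

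The conclusion on the headcount rests on reading the 10% as a share of the patients recruited, which is the ordinary meaning and the only one that the article offers. The conclusion on power rests on the plan's difference and SD and on holding the implied design effect of 4.02 fixed. It also takes 692 as given. That figure was not reproduced from the ICC, cluster size and number of steps: the simple parallel design effect gives 172 x 3.28 = 564, and the stepped-wedge variants tried gave about 486 to 649. Because the article does not state its formula and the design figure is not shown, nothing is concluded from this, and the drop-out point does not depend on it.

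**What to change.** Low priority. Either of two edits to the Sample size section is enough.

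- Keep 762 and add that, at 10% drop-out, it yields about 686 evaluable patients (about 343 per group), with about 90% power under the plan's own inputs. This needs one sentence and no extra recruitment.
- Or correct the inflated figure to 769, or to 770 with 385 per group, and change 381 to 385 in the peer paragraph. The 77 and 88 peers stay as they are. If the target is actually raised, this means 7 to 8 more patients, about one per department.

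The first option is sufficient and costs least.

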### Data analysis

#### Quantitative outcomes analysis

The statistical analysis will be performed on the intention-to-treat population. The statistical significance will be a two-sided alpha level of 5%. Statistical analyses will be performed using SAS software (SAS-Windows version 9.4 on computer PC) and R software version 4.2.1 on computer. The characteristics of the population will be described using quantitative variables, including the mean and SD, and qualitative variables, such as the number of cases and percentages. The Acti-Pair programme’s effect on the PA level will be analysed using a mixed-effects model with a random intercept per department to consider the correlation of the level of PA between patients of the same department and a random effect on the initial value of PA. This random effect will depend on both the cluster and the patient (random effect of the patient nested in the cluster). The model will consider the fixed effect of the treatment group (Acti-Pair programme or usual care). The possible evolution of the evaluation criterion over time will be analysed by introducing a calendar time variable into the mixed-effects regression model (5 periods of 6 months, see figure 3). If a trend is identified, the calendar time variable can be introduced into the model as an ordinal variable. This analysis will make it possible to quantify the effect of the Acti-Pair programme after adjustment for a possible time effect. An interaction between the effect of the treatment group and the random ordinal by the department may be added to quantify any heterogeneity in the benefit of the Acti-Pair programme. An initial model will be built without additional adjustment. If an imbalance between the groups is observed, a second model will be built by adjusting the variable(s) on which the imbalance is observed (sensitivity analysis). A possible logarithmic transformation of the evaluation criterion could also be considered to satisfy the normality assumption of the linear mixed-effects model.

For the analysis of the secondary endpoints, no p value will be given, and only the 95% CIs of the efficacy indices will be estimated.^28^ It will be carried out using a mixed-effects model similar to the one used for the primary endpoint. No interim analysis is planned.

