**Social support**For 12 months	**Aim:** establishing a supportive relationship with participating patients. Assessing their level of motivation. Monitoring their PA. Identifying healthcare problems and resolving barriers to regular PA. **How?** Regular communication with patients. Conducting PA sessions with patients. Offering tailored advice to help patients overcome barriers to achieving their PA goals.
**Personalised and realistic project**For 12 months	Supported by DAPAPs PA check-up. Motivational, needs and constraints assessments by APA professionals.
**Support from professionals**For 12 months	PA prescription by HP. Follow-ups at 3, 6 and 12 months by APA from DAPAPs: PA assessments, reviewing the patient’s PA project, verifying that the established objectives have been met and re-evaluating them as needed. Communication between DAPAP and HP about assessment results and all actions to implement the patient’s PA plan.

APAadapted physical activityDAPAPsDevices for Adapted Physical Activity PracticeHPhealth professionalsMETmetabolic equivalent of taskPAphysical activity

The Acti-Pair programme for patients is illustrated in figure 2.

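### The primary model has no term for the peer who supports up to five Acti-Pair patients, so if outcomes correlate within peer the standard error is modestly understated

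*Protocol article*

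**What the plan says.** Three parts of the Protocol article bear on this point.

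- **Sample size** puts Acti-Pair patients in groups: "Each peer will follow a maximum of 5 patients (Acti-Pair pilot study), and 381 patients will be followed (interventional group), that is, 77 peers". After an allowance for drop-out, 88 peers are to be recruited, 11 per department. The only clustering allowed for is a department ICC of 0.04.
- **Table 1** (Social support) gives the peer 12 months of contact with his patients. His tasks include monitoring their activity, giving tailored advice and "Conducting PA sessions with patients". Controls have no peer.
- **Quantitative outcomes analysis** fixes the random effects. There is an intercept per department, and an effect on the initial activity value: "This random effect will depend on both the cluster and the patient (random effect of the patient nested in the cluster"). A treatment-by-department heterogeneity term is optional. On the secondary endpoints it says: "It will be carried out using a mixed-effects model similar to the one used for the primary endpoint". These are reported as 95% confidence intervals without p values.

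**The concern.** Peers exist only in the intervention stage, so the design is partially nested: controls are grouped by department, Acti-Pair patients by department and by peer. Men who train with the same peer for a year may end up more alike than men in the same department with different peers.

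Neither stated random effect can carry that likeness. The department intercept is shared by control and Acti-Pair patients and by all the department's peers. The patient effect belongs to one man and cannot link two.

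If the peer ICC is above zero, the model counts more independent information in the Acti-Pair arm than there is. The primary test would then reject somewhat more often than 5% under the null, and the secondary intervals would cover less than 95%.

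**Working it through.** **1. The plan's own figures.** Sample size assumes "5.5±4 MET-hours/week in the usual care group and 7.5±4 MET-hours/week in the Acti-Pair group", alpha 5% and power 90%.

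- Normal approximation: n = 2 × (1.960 + 1.282)² × 4² / 2² = 84.06, so 85 per group. The t-based calculation gives 86 (power 0.903), which agrees with "it is necessary to include 86 patients per group, that is, 172 in total".
- Peers: 381 / 5 = 76.2, so 77. With drop-out, 77 / 0.9 = 85.6, so 86; rounding up to 11 in each of 8 departments gives 88.
- Patients per peer: 381 / 77 = 4.95 enrolled; 346 / 77 = 4.49 analysed.

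**2. Simple design-effect check.** With m patients per peer and peer ICC ρ (assumed, as none is given), the Acti-Pair arm's variance is inflated by DE = 1 + (m − 1)ρ. With equal arms, true SE / model SE = √((1 + DE)/2), and actual alpha = 2Φ(−1.96 / ratio). For m = 5:

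| ρ | DE | SE ratio | alpha |
|---|---|---|---|
| 0.01 | 1.04 | 1.010 | 5.2% |
| 0.02 | 1.08 | 1.020 | 5.5% |
| 0.05 | 1.20 | 1.049 | 6.2% |
| 0.10 | 1.40 | 1.095 | 7.4% |

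With m = 4.49 the ratios at 0.05 and 0.10 are 1.043 and 1.084.

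**3. Stepped-wedge calculation.** Figure 3 is not shown, so the layout is assumed: sequences CTIII, CCTII and CCCTI (C control, T transition, I intervention), 8 departments, 22 patients per recruiting department-period (704 in total), period effects fitted, SD 4, department ICC 0.04, difference 2, five patients per peer, 12-month value only.

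Let V₀ be the covariance with department and residual only, and V₁ the same with peer variance ρ × 16 added among Acti-Pair patients sharing a peer (total SD kept at 4). The reported variance is the treatment element of A = (X′V₀⁻¹X)⁻¹; the true variance is that of A X′V₀⁻¹V₁V₀⁻¹X A. Type I error = 2Φ(−1.96 × reported SE / true SE).

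| Departments per sequence | ρ | reported SE | true SE | SE too small by | type I error |
|---|---|---|---|---|---|
| 3/3/2 | 0.01 | 0.861 | 0.867 | 0.7% | 5.2% |
| 3/3/2 | 0.02 | 0.861 | 0.874 | 1.4% | 5.3% |
| 3/3/2 | 0.05 | 0.861 | 0.892 | 3.5% | 5.9% |
| 3/3/2 | 0.10 | 0.861 | 0.922 | 6.6% | 6.7% |
| 3/2/3 | 0.01 | 0.774 | 0.781 | 0.9% | 5.2% |
| 3/2/3 | 0.02 | 0.774 | 0.788 | 1.7% | 5.4% |
| 3/2/3 | 0.05 | 0.774 | 0.808 | 4.2% | 6.0% |
| 3/2/3 | 0.10 | 0.774 | 0.840 | 7.9% | 7.1% |

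The remaining split, 2/3/3, gives slightly more: 0.861 against 0.947 at ρ = 0.10, or 9.1%.

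Power, Φ(2/SE − 1.96), compares the stated model with one that contains the peer term. At ρ = 0.05 it falls from 64.2% to 61.2% (3/3/2) or from 73.4% to 69.9% (3/2/3). At 0.10 it falls to 58.7% or 66.8%.

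**4. Simulation.** The department-intercept model was fitted by REML to the 3/3/2 layout, 2,000 runs per setting. Null rejection was 5.5%, 7.4%, 6.7% and 7.8% at peer ICC 0, 0.02, 0.05 and 0.10. Monte Carlo error is about 0.5 points, which explains the lack of order in the middle. The department intercept does not absorb the peer effect.

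**The case against.** **The harm is conditional and small.** This stands. The article gives no peer ICC for 12-month activity. At zero nothing is lost, and at 0.01-0.02 the type I error barely moves. Five per peer is a maximum. The low-ICC simulation results are hard to separate from noise, so the size rests on the analytic calculation.

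**Patients sharing a peer are not treated as fully independent.** Correct: the department intercept already correlates them. They are independent only given department.

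**The optional treatment-by-department term may help.** It could absorb part of the peer variance. But the plan does not commit to it, it would be estimated from eight departments, and it is not a peer term.

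**Dependence on peers is studied elsewhere.** The process evaluation, alliance and satisfaction scales and interviews address how the programme works, but none corrects the standard error.

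**Other uncertainties are larger.** Under the assumed layout the stated model has 64-73% power against the planned 90%, before any peer effect. That gap depends on a figure that is not shown and is no part of this point.

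**This could be left to an analysis plan.** That would be a fair answer if the article were silent. It states which random effects the model has, and a planned level of grouping is not among them.

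**Conclusion.** The point holds in conditional form. The article plans the grouping by peer and states a model that leaves it out. Any positive within-peer correlation makes the standard error too small: by about 1-2% at a peer ICC of 0.01-0.02, about 4% at 0.05 and about 7-8% at 0.10, slightly less with about 4.5 analysed patients per peer. These sizes rest on assumed peer ICCs and an assumed layout; the direction does not.

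A reader might infer three stronger things that the documents do not support:

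- *That the primary test is invalid.* This needs a material peer ICC, which is not given.
- *That a few unusual peers could drive the result.* One peer covers at most 5 / 381 = 1.3% of the arm.
- *That peer support is the thing under test.* The objectives concern a three-component programme, of which it is one part.

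**What to change.** In **Quantitative outcomes analysis**, add to the primary model and to the similar secondary models a random effect of peer nested in department, applying to Acti-Pair patients only, with each control as his own unit. Group by the peer first assigned, to keep to intention to treat. Report the peer ICC with its confidence interval. Arm-specific residual variance is optional, if the model supports it.

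In **Data collection**, state that the patient-peer link is recorded in the e-CRF. Peers already have e-CRFs for follow-up costs, so the link is probably obtainable, but the article does not say so and the sponsor should confirm it.

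In **Sample size**, state that the ICC of 0.04 covers department only, and show power over a peer ICC range of 0 to 0.10.

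**Cost:** no extra patients or visits. The confidence interval will be slightly wider and the stated power slightly lower. The peer variance may be estimated near zero, so the plan should say what is done in that case.

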## Study design

This is a pragmatic stepped-wedge randomised controlled study of the Acti-Pair programme implementation in eight French departments, that is, eight clusters, each composed of one DAPAP, operating in the area defined by the department it is located. The intervention will be deployed in a random order, successively in the various clusters, across three stages (control, transition and interventional stages). First, all clusters start in the control and sequentially transition into the intervention (the Acti-Pair programme) until all clusters have received the intervention. Participants will be recruited successively in patients' control and intervention stages and the transition stage for peers.

The stepped-wedge design is presented in figure 3.

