### Randomisation

Each cluster will be randomly allocated to one of three sequences (two or three clusters per sequence (see figure 3)). The cluster phase allocation (Acti-Pair programme vs usual practice) will be performed by centralised randomisation via an internet platform (EnnoV Clinical software). The randomisation list will be a pseudorandomised computer list developed by a statistician before the beginning of the study. Randomisation will be stratified by cluster size. Due to the behavioural nature of the intervention, this study will not be blinded. However, the risk of bias for the primary objective assessment will be reduced because PA will be measured objectively.

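### Departments are randomised within cluster-size strata, but the initial primary model is stated to carry no additional adjustment, so the stratum can enter only a sensitivity model; the loss is small and cheap to remove

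*Protocol article*

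**What the plan says.** Randomisation (protocol article): "Each cluster will be randomly allocated to one of three sequences (two or three clusters per sequence"; and "Randomisation will be stratified by cluster size". Size is thus the one named factor that restricts the allocation of the eight departments.

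Quantitative outcomes analysis: the primary analysis is a "mixed-effects model with a random intercept per department", together with "a random effect on the initial value of PA" (patient nested in cluster). For treatment, "The model will consider the fixed effect of the treatment group (Acti-Pair programme or usual care"). Calendar time, in five six-month periods, may be added if the data show a trend, and a treatment-by-department interaction may be added to describe heterogeneity. Then: "An initial model will be built without additional adjustment". A second model, labelled a sensitivity analysis, adjusts for whichever variables turn out to differ between the groups. Secondary endpoints use a similar model. Cluster size is named in none of these.

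Study design: "all clusters start in the control and sequentially transition into the intervention (the Acti-Pair programme) until all clusters have received the intervention". Every department is therefore planned to supply both control and intervention patients.

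**The concern.** An analysis normally conditions on the factors used to restrict the randomisation. Here a stated rule keeps the stratifier out of the initial model, and it can return only through a check of observed imbalance. That makes the handling of a known design factor depend on the data.

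The random department intercept covers this only in part. It treats any size-related difference between departments as random and leaves it in the variance. A random-intercept stepped-wedge estimator also draws some information from comparisons between departments. Nor can stratification balance size exactly: if there are two size strata, a sequence of three departments cannot be split evenly between them.

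If size is related to MVPA, the primary standard error is somewhat larger than it need be, and the estimate carries a small shift from the size mix across sequences. The article does not say whether size and MVPA are related.

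**Working it through.** **The plan's own figure.** For a difference of 7.5 − 5.5 = 2.0, SD 4, two-sided 5% and 90% power, n per group = 2 × (1.960 + 1.282)² × 4² / 2² = 84.1, so 85. The t-based version gives 86, as the Sample size section states. The present point does not rest on that figure. It supplies the SD and the target difference used below.

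**Inputs from the article.** SD 4, so total variance 16. ICC 0.04, so between-department variance τ² = 0.04 × 16 = 0.64 and within-department variance 15.36. 692 patients before drop-out, eight departments, three sequences, five periods.

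**Assumptions (not in the article).** Figure 3 is not shown, so with C control, T transition (no patients recruited) and I intervention, the sequences were taken as CTIII, CCTII and CCCTI, with 3, 3 and 2 departments. Two size strata of four departments, large ones twice the size of small ones. Patients spread evenly over each department's recruiting periods. The share R² of between-department variance explained by size was varied from 0 to 75%. The initial-activity term was left out of the calculation.

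**Method.** Generalised least squares on the department-period means. The variance of the treatment effect is the treatment element of (X′V⁻¹X)⁻¹, where V has 15.36/n on the diagonal plus τ² within a department. Without the stratum τ² = 0.64. With the stratum as a fixed effect τ² = 0.64 × (1 − R²).

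**With period effects** (standard error without the stratum 0.853; power for a difference of 2.0 is Φ(2/0.853 − 1.96) = 65.0%):

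| R² | SE with stratum | SE ratio | Variance ratio | Power |
|---|---|---|---|---|
| 0 | 0.854 | 1.00 | 1.001 | 64.9% |
| 25% | 0.846 | 0.99 | 0.982 | 65.7% |
| 50% | 0.833 | 0.98 | 0.953 | 67.0% |
| 75% | 0.810 | 0.95 | 0.902 | 69.4% |

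**Without period effects** (equal department sizes): the standard error is 0.318 without the stratum and 0.318, 0.317, 0.315 and 0.310 with it, a reduction of at most 2.5%. Power is essentially 100% in each case, since 2/0.318 is about 6.3.

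**Sensitivity to the layout.** With 2, 3 and 3 departments per sequence, or with equal or threefold department sizes, the ratios change by a few tenths of a percentage point.

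**Shift from unequal size mix.** The stratum difference implied by R² is 2 × √(0.64 × R²), that is 0.80, 1.13 and 1.39 MET-hours/week at 25%, 50% and 75%. In the layout above, with period effects, the estimator without the stratum puts a net weight of about 0.048 on the stratum indicator. The shifts are therefore 0.048 × 0.80 = 0.04, 0.048 × 1.13 = 0.05 and 0.048 × 1.39 = 0.07. Other near-balanced allocations give the opposite sign, and the largest absolute value found was 0.08. Without period effects the shift is about 0.02 at most.

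**The case against.** The strongest case for leaving the plan alone has five parts.

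- **The effect is estimated mostly within departments.** Size is constant within a department, and each department contributes both conditions, so the parallel-group argument for adjusting by stratifiers carries over only weakly. This stands, and it is why the figures are small.
- **The premise is not in the article.** Nothing there says that size predicts MVPA. The stratification may serve only to even out patient numbers across sequences. This also stands: at R² = 0 the change gains nothing.
- **A degree of freedom is costly with eight departments.** If inference rested on between-department degrees of freedom falling from 6 to 5, the critical value would rise from 2.447 to 2.571, about 5%, and would cancel the gain. This does not stand for a model of this type. Treatment varies within departments, and in a REML simulation the Satterthwaite degrees of freedom for the treatment effect stayed above 100 in every scenario. The same simulation showed power barely changing, which supports calling the point minor.
- **The analysis plan may settle it.** It may add detail, but the article does more than stay silent. It says the initial model has no additional adjustment, and a plan that put the stratum in that model would contradict it.
- **Conditional calendar time matters far more.** In the assumed layout with equal department sizes, period effects move the standard error from 0.318 to 0.868. That is true, but it is a separate issue.

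Three stronger readings are tempting, and the documents do not support them. The first is that the benefit of stratifying is thrown away: balance comes from the allocation and remains whatever the model contains. The second is that the estimate is systematically biased: the shift is a chance feature of the allocation drawn. The third is that the model is only treatment plus a department intercept: the article also gives the initial-activity term, conditional calendar time and the adjusted sensitivity model.

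**Conclusion.** The mismatch is real: the randomisation is stratified by cluster size, and the initial model is stated in a way that leaves the stratum out. It is minor. The standard error would fall by 0 to about 5% with period effects and by 0 to about 2.5% without. The chance shift removed is at most about 0.07 to 0.08 MET-hours/week, roughly 8 to 9% of a standard error of about 0.85 and 4% of the 2.0 target. These sizes depend on the assumed layout, two strata and the assumed share of variance explained by size, none of which the article gives. The case for the change rests less on the gain than on analysing by the groups within which the trial randomises, without an observed-imbalance trigger, at almost no cost.

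**What to change.** In the section on quantitative outcomes analysis, state that the initial model includes the cluster-size stratum used in the randomisation as a fixed effect, with no other additional adjustment. Apply the same term in the matching secondary-endpoint models. Keep the model without the stratum as a prespecified sensitivity analysis. If the sponsor prefers to leave the stratum out of the initial model, give the reason.

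The cost is one sentence. No new data are needed, because the stratum is known at randomisation. Statistically it uses one between-department degree of freedom and adds about 0.1% to the variance if size is unrelated to MVPA.
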